## Abstract

**Background:**

Treatment burden is the effort required of patients to look after their health and the impact this has on their functioning and wellbeing. It is likely treatment burden changes over time as circumstances change for patients and health services. However, there are a lack of population-level studies of treatment burden change and factors associated with this change over time. Furthermore, there are currently no practical screening tools for treatment burden in time-pressured clinical settings or at population level.

**Methods and analysis:**

This is a three-year follow-up of a cross-sectional survey of 723 people with multimorbidity (defined as three or more long-term conditions; LTCs) registered at GP practices in in Dorset, England. The survey will repeat collection of information on treatment burden (using the 10-item Multimorbidity Treatment Burden Questionnaire (MTBQ) and a novel single-item screening tool), sociodemographics, medications, LTCs, health literacy and financial resource, as at baseline. Descriptive statistics will be used to compare change in treatment burden since the baseline survey in 2019 and associations of treatment burden change will be assessed using regression methods. Diagnostic test accuracy metrics will be used to evaluate the single-item treatment burden screening tool using the MTBQ as the gold-standard. Routine primary care data (including demographics, medications, LTCs, and healthcare usage data) will be extracted from medical records for consenting participants. A forward-stepwise, likelihood-ratio logistic regression model building approach will be employed in order to assess the utility of routine data metrics in quantifying treatment burden in comparison to self-reported treatment burden using the MTBQ.

**Impact:**

To the authors’ knowledge, this will be the first study investigating longitudinal aspects of treatment burden. Findings will improve understanding of the extent to which treatment burden changes over time for people with multimorbidity and factors contributing to this change, as well as allowing better identification of people at risk of high treatment burden.

## Introduction

Treatment burden is the effort required of patients to look after their health and the impact this has on their functioning and wellbeing [1–4]. Taking and managing multiple medications, organising and attending healthcare appointments, monitoring health, performing self-care, and modifying lifestyle behaviours all contribute to this workload [3]. In addition, patients may experience adverse effects of medications, drug-drug interactions and drug-comorbidity interactions [5]. The need to assess treatment burden in the context of multimorbidity (defined in this study as the presence of three or more long-term conditions) was recognised in the National Institute for Health and Care Excellence (NICE) 2016 guidance for the assessment and management of multimorbidity [6]. People with few chronic conditions, whose treatment is straightforward, may have a treatment workload that is justifiable and well tolerated. For those with greater clinical complexity and fewer available resources, total workload of a treatment regimen might represent a substantial burden, outweighing patient ‘capacity’ (ability to manage workload conferred by both treatment and the demands of everyday life) and risk treatment failure [7].

Treatment burden may be exacerbated by the predominance of single-disease-focused clinical guidelines, with patients often asked to follow multiple treatment plans in parallel [8]. Patients with complex disease and/or multimorbidity may feel overburdened, resulting in low treatment adherence, worse health outcomes and poor quality of life [9–13]. This, in turn, may contribute to health service inefficiency and ineffectiveness, healthcare inequity, and has led to calls for health services to be organised in ways that are as straightforward and holistic as possible for patients and carers, such that care is prioritised from the patient perspective [14, 15]. This is important given the ageing and increasingly multimorbid UK population [16]. Our previous cross sectional study of treatment burden among older people (≥55years) with multimorbidity (defined as having three or more long-term conditions from a specified list) [17] in the county of Dorset, England found that approximately one in five people experience high treatment burden and that high treatment burden was associated with limited health literacy, financial difficulty, having more long-term conditions and greater number of prescribed regular medications [18]. However, for commissioners and those planning service delivery for people with complex needs, no population-level longitudinal studies exist that give an indication of the extent to which treatment burden changes over time. In addition, little is known about the factors (both individual and system-driven) associated with change in treatment burden over time. At health system level, interventions that reduce treatment burden and foster ‘minimally disruptive medicine’ may lead to efficiencies and improve quality of care as well as improving patients’ quality of life [19]. Healthcare systems will also need to consider how to identify people at risk of being overburdened [20]. At the individual patient-clinician level, assessing the degree of treatment burden allows for discussion with patients about optimising treatments and care,–balancing the management priorities of different conditions, and exploring if total healthcare workload is compatible with patients’ daily lives. Several quantitative measures of treatment burden have been developed and validated [21–28]. However, routinely measuring treatment burden using current questionnaire measures is not practical in most clinical settings, even employing those tools with fewer items [22]. At system level, being able to identify those at risk of being overburdened via routinely collected data would assist with care planning.

This protocol describes a follow-up survey study of 723 people aged 55+ years with multimorbidity in Dorset, England, who took part in the baseline survey and consented to complete a follow-up survey within three years. The baseline survey was conducted between February and July 2019, prior to the COVID-19 pandemic [18]. Dorset health and social care provision underwent a large-scale Clinical Services Review prior to 2019 and reconfiguration of services delivering care to people with LTCs has been implemented since the baseline survey [29]. This follow-up survey is expected to be conducted between August and October 2021.

## Materials and methods

### Aims and objectives

This follow up cross-sectional survey of people with multimorbidity will quantify change in treatment burden over time and evaluate factors associated with treatment burden change. The survey will also facilitate evaluation of the validity of a single-item treatment burden question, modified from an item originally trialled in the baseline survey. Survey-measured, self-reported treatment burden will be compared to routine primary care metrics and the feasibility of developing a risk tool for high treatment burden based on routine data will be explored. The protocol described in this peer-reviewed article is published on protocols.io, https://dx.doi.org/10.17504/protocols.io.bw5fpg3n and is included for printing as S1 File with this article.

The objectives of the study are to:

Explore the degree to which treatment burden changes over time and the factors associated with such change.Evaluate the validity of a single-item treatment burden screening tool versus high treatment burden at follow-up.Undertake descriptive comparison of survey-measured, self-reported treatment burden with relevant metrics extracted from the primary care records of surveyed patients who provide consent for this aspect.Develop and test the internal validity of a high treatment burden predictive risk tool for use in primary care/commissioning settings to identify those at risk of high treatment burden using metrics from routine clinical data of those surveyed, in comparison with survey-measured self-reported treatment burden. If secondary care data are available, then use this to further enhance the risk tool.Explore whether there is any relationship between our measured change in treatment burden and the reconfiguration of services in Dorset.

### Ethics

This study protocol has received Research Ethics Committee approval (reference: 21/EM/0021) and Health Research Authority (HRA) approval (IRAS project ID: 292906) on 27 January 2021.

### Study sites and participants

All eight GP practices who took part in the baseline study will be approached to assist with this follow-up study. These practices were selected to represent a mixture of urban and rural, affluent and more deprived locations across Dorset. A flowchart of the methods and analysis is presented in S1 Fig.

Study participants will be patients within these practices who took part in the baseline survey and consented to receiving the follow up survey (n = 723). The original inclusion criteria of the baseline survey were those aged 55 years or over and living with at least three of the following LTCs: atrial fibrillation, coronary heart disease, heart failure, hypertension, peripheral arterial disease, stroke or transient ischaemic attack, diabetes, asthma, chronic obstructive pulmonary disease, depression, chronic kidney disease, epilepsy, osteoporosis, rheumatoid arthritis, Parkinson’s disease, multiple sclerosis, inflammatory bowel disease, coeliac disease, osteoarthritis. We defined multimorbidity as three or more chronic conditions for the following reasons: (i) to be consistent with the baseline study, (ii) the sample size calculation was based on the prevalence of a previous study which used this definition, and (iii) this has been considered to be a more valid cut-off score than the criterion of two chronic conditions for multimorbidity in elderly patients [30]. The specified diseases were selected as they are common, readily identified from GP records, and represented a range of body systems. Diseases were defined using the Quality and Outcome Framework (QoF) clinical code and Read codes [22, 23, 31, 32]. Only one person from a given household was eligible to participate [18]. Exclusion criteria were: those living in a care home, receiving palliative care, presence of a mental health diagnosis (psychosis, schizophrenia, bipolar disorder) or dementia, active cancer (recorded in the last three years), an expressed wish not to participate in research, lack of capacity to participate in the study, or any other reason at the discretion of healthcare professionals at the GP practice with sufficient knowledge of the patient which renders the patient unsuitable to receive the survey (for example if they were very frail, having cancer investigations, had a very recent bereavement It was not considered ethically appropriate or acceptable to send the survey out to patients who met the exclusion criteria as they might find it particularly distressing. Each participating site applied the same algorithm to electronically search and identify potential participants. Manual screening was performed by a health professional to exclude patients that met the exclusion criteria. A maximum of 250 patients (randomly selected from all potentially eligible participants) from each practice were invited to participate in the baseline survey.

### Participant recruitment and invitation

Participating practices will be asked to identify the patients who were participants in the baseline survey and consented to receiving the follow-up survey, using a list of unique study IDs. Lists of these potentially eligible patients will be manually screened by GPs (or another suitable healthcare professional with sufficient patient knowledge from the GP practice) for exclusion criteria (as some participants may now meet the exclusion criteria). Practices will be encouraged to only exclude people if they feel it is absolutely necessary, while acknowledging that in some circumstances, sending the follow-up survey may be inappropriate.

#### Survey pack mail out

The research team will prepare survey packs (containing a participant information sheet, carbon duplicate consent form, survey booklet, two pre-addressed freepost return envelopes, and a £5 gift voucher as an incentive), having affixed study ID labels to survey and consent forms. These prepared survey packs will be supplied to GP practices, who at the point of invitation will: (i) add a prepared covering letter to the pack (headed up and signed by the GP practice), personalising the letter with the invitee’s name and address; (ii) add the invitee’s name and address to the outer envelope of the survey pack. Patient details and study IDs will be matched in accordance with practices’ research records. Practices will post out survey packs on behalf of the research team. Recipients will be asked to complete the paper consent form and paper survey booklet and return both by post in the separate envelopes provided within one month of receiving the survey pack. An online response platform is not being provided for this follow-up survey as a result of the very low uptake of this response option (3.2%) observed in the baseline survey.

### Survey items

For this follow-up survey, changes from the baseline survey design are minimal in order to provide maximally comparable follow-up data from that acquired at baseline. Survey questions and response options of the baseline survey are available elsewhere [18].

#### Outcomes

The survey will measure self-reported treatment burden using the 10-item Multimorbidity Treatment Burden Questionnaire (MTBQ [22]. The MTBQ is short, simple, and easy to use and has been validated in a multimorbid population similar to that in the current study. It has demonstrated good validity, reliability and responsiveness. Scores for each MTBQ item range from 0 (not difficult/does not apply) to 4 (extremely difficult). The average score is multiplied by 25 to yield a score ranging from 0 to 100 and then categorised to non (global score of 0), low (>0 and <10), medium (≥10 and <22), or high (≥22). A novel single-item screening tool for treatment burden that was developed together with our public contributors will also be included in the survey, in place of the original exploratory single-item measure included in the baseline survey. This novel single-item tool asked: “Have you felt overstretched by everything you’ve had to do to manage your health in the last month (e.g., taking medicines, getting prescriptions, attending appointments)?” to which participants could respond ‘yes’ or ‘no’.

#### Exposures

Prescribed regular medication, number of (and specific) LTCs based on survey inclusion criteria, travel for healthcare, recent healthcare resource use, and health status/quality of life (measured using the Short form-12 Health Survey (SF-12)) will also be collected.

#### Potential confounders

Sociodemographic information including age (as a continuous variable), sex (male/female), marital status (married or in a civil partnership, single (never married or in a civil partnership), divorced or dissolved civil partnership, widowed) were collected in the survey.

#### Potential effect modifiers

Level of education (not asked at baseline) based on the following categories: NVQ4/NVQ5/Degree or equivalent, NVQ3/GCE A Level equivalent/4 NVQ2/GCE O Level equivalent/5NVQ1/CSE other grade equivalent, or no qualification; home ownership (home owner/non-home owner); capacity to manage health such as financial resources [perceived level of difficulty in meeting financial costs of healthcare (on a 5-point Likert scale from ‘no’ to ‘extreme’ difficulty)] and health literacy [assessed using the Single Item Literacy Screener (SILS) which measures perceived frequency of needing help to read health-related written material (on a 5-point Likert scale, where ‘sometimes’, ‘often’ and ‘always’ indicate limited health literacy] were also asked in the survey as they may be expected to modify the relationship between exposures and treatment burden.

### Data extraction from primary care records

Data from primary care records will be extracted for respondents who consent to data from their GP record being shared with the research team. Extracted data will include: demographic details (current age, sex, full postcode) as recorded in primary care records, frailty score (electronic Frailty Index and/or Rockwood score where available), main diagnosed health conditions as defined by Read codes, medications on repeat prescription (including details of dose, frequency, and route of administration), recent healthcare usage data (including number of GP practice appointments by type -surgery appointment, telephone consultation, home visit- and role (GP, practice nurse, or other team member), number of outpatient appointments/referrals to secondary care, accident and emergency attendance (if available) and hospital admission data (a count of discharge summaries), as available in the primary care record. We will discuss with colleagues in the CCG about the potential for enhancing primary care data with data from secondary care. These variables have been selected as they may be expected to be associated with high treatment burden.

#### Minimising potential bias

To reduce selection bias, we invited all patients who took part in the baseline survey and consented to receiving a follow-up survey to take part in the current study. This sample includes participants from a range of practices (urban vs rural) socioeconomic background, geographical location. Furthermore, all participants will be treated the same way (i.e., they will receive the same survey asking same questions/measures and be asked to be returned the survey in same way). The same algorithm will also be used across all practices to extract routine data in order to reduce measurement bias.

### Sample size

The pool of participants is limited to the 723 individuals who consented to receiving the follow-up survey. The sample size of the baseline survey was determined using nQuery based on prevalence of high treatment burden (26.6%) from the validation study of the MTBQ together with estimates of likely response rate of approximately 50% (based on the literature) and distribution of the MTBQ score [18]. It was estimated that a minimal sample size of 150 participants would be needed to detect the minimum possible change in treatment burden score (1 point in the 40-point MTBQ raw score) over time. A follow-up sample of 361 participants is anticipated, assuming a likely follow-up survey response rate response rate of 50%.

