### Statistical analyses

Descriptive statistics will be used to compare the numbers and proportions of participants reporting ‘none’, ‘low’, ‘medium’ and ‘high’ levels of treatment burden based on the global MTBQ score (score of 0, <10, ≥10, ≥22, respectively). We will consider those who report a ≥1 point change in the 40-point MTBQ raw score as having experienced a change in treatment burden, though we recognise this change may not be clinically meaningful. Change in global score and change in these categories between baseline and follow-up will be compared. Characteristics (such as age, sex, education status, and comorbidities) of participants who experience change in treatment burden, those who experience an increase in treatment burden, those who experience a decrease in treatment burden and those who don’t will be described. We will also describe and compare characteristics of those who have experienced an increase in treatment burden to those who have not and those who have experienced a decrease in treatment burden to those who have not. Normally distributed variables will be compared using t-test and categorical variables will be compared using chi-squared tests. Associations with change in categories of treatment burden (i.e., overall change vs no change; decrease vs no change or increase; increase vs no change or decrease) will be examined using a linear mixed model that additionally adjusts for potential confounders. We will also examine effect modification using interaction terms. We will also explore geographical access aspects of treatment burden, considering issues such as distance and travel time to GP and hospital services and distance /time from pharmacies (and/or whether individuals are registered with dispensing practices). Further consideration will be given to availability of public transportation for any of these services. Distance to services for this population may be contrasted with access to treatment for similar age/sex populations in other areas of Dorset to assess whether there is significantly better/worse service provision for the study population. Regressions will adjust for time (year) to account for (and explore impact of) changes to services in Dorset.

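### The figure of 150 covers only the mean change in score over time; the factors of change are examined on three yes/no contrasts that discard information, one of which pools worsening with improvement

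*Protocol article*

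**What the plan says.** Objective 1 has two parts: "Explore the degree to which treatment burden changes over time and the factors associated with such change".

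The Sample size section gives one required number for change, a "minimal sample size of 150 participants would be needed to detect the minimum possible change in treatment burden score", with that change put at 1 point on the 40-point raw score, over time. It adds that "The pool of participants is limited to the 723 individuals who consented to receiving the follow-up survey" and, at a 50% response, "A follow-up sample of 361 participants is anticipated". The other input named there, "based on prevalence of high treatment burden (26.6%) from the validation study of the MTBQ", belongs to the size of the baseline survey.

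Under Statistical analyses, the definition of change is: "We will consider those who report a ≥1 point change in the 40-point MTBQ raw score as having experienced a change in treatment burden". The same sentence grants that this may not be clinically meaningful. Associations with change are then to be examined on three contrasts, "overall change vs no change; decrease vs no change or increase; increase vs no change or decrease", in a linear mixed model adjusted for confounders. Interaction terms are also planned.

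**The concern.** The stated number and the association analysis answer different questions. Detecting a mean shift of 1 point in the same people is a paired comparison of a score. Asking whether change differs between people with and without a factor is a between-group comparison, and here it is made on outcomes cut from the score.

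Sensitivity is lost at three points. For two equal groups, a between-group difference needs about four times the total number that a paired shift of the same size needs. Reducing a signed score to increase or not, or decrease or not, discards how far each person moved. And overall change against no change joins opposite directions: a factor that raises burden produces more increasers and fewer decreasers, and the two nearly offset.

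At stake is how null results are read. A factor that shows nothing on overall change could be reported as unrelated to change when the outcome was hardly able to show it.

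**Working it through.** **Inputs from the protocol article.** 150, 1 raw point, and 723 × 0.5 = 361.5, given as 361 (Sample size). Change at 1 raw point or more, and three yes/no contrasts (Statistical analyses).

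**Assumptions, because the article gives no figure.** Two-sided 5% and 80% power behind the 150, with 90% power and one-sided 5% as variants. A 1-point difference in mean change between groups, borrowed from the only effect size the article names. Factor splits from 50:50 to 20:80. Change roughly normal and in whole points, so the cuts lie at ±0.5. Reference-group mean change 0 unless stated.

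**1. The plan's own figure.** For a paired mean, n = (SD × (z_α + z_β) / δ)². With no SD stated, 150 cannot be reproduced, only inverted: SD = √150 / (z_α + z_β).
- Two-sided 5%, 80% power: 12.25 / 2.802 = 4.37 (back-check (4.37 × 2.802)² ≈ 150)
- Two-sided 5%, 90% power: 12.25 / 3.242 = 3.78
- One-sided 5%, 80% power: 12.25 / 2.486 = 4.93

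**2. Mean change over time, N = 361.** SE = 4.37 / 19 = 0.230. Power = Φ(1/0.230 − 1.96) = 99%. Over the three SDs it is 97% to 99.9%. For this question 361 is ample.

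**3. Between groups, continuous change.** SE = SD × √(1/n₁ + 1/n₂). At 50:50, SE = 4.37 × 2/19 = 0.460 and power = Φ(1/0.460 − 1.96) = 58%. At 20:80, SE = 4.37 × 2.5/19 = 0.575 and power is 41%.

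**4. Increase or decrease against the rest, SD 4.37, 50:50, means 0 and 1.**
- Increase: 1 − Φ((0.5 − μ)/4.37) gives 45.4% and 54.6%. Null SE 0.0526, alternative SE 0.0524, so power = Φ((0.091 − 1.96 × 0.0526)/0.0524) = 41%.
- Decrease: Φ((−0.5 − μ)/4.37) gives 45.4% and 36.6%. Power 40%.

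**5. Overall change.** The 1-point shift adds about 9 percentage points of increasers and removes about 9 of decreasers. The share with any change is 90.9% against 91.1%, and power is 5%. This is not a shortage of people: 10,000 participants would give about 7%.

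**6. Range at N = 361 (power, %).**

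| Outcome | Split | SD 3.78 | SD 4.37 | SD 4.93 |
|---|---|---|---|---|
| Continuous change | 50:50 | 71 | 58 | 49 |
| Increase / decrease | 50:50 | 52 / 51 | 41 / 40 | 34 / 33 |
| Continuous change | 20:80 | 52 | 41 | 34 |
| Increase / decrease | 20:80 | 36 / 34 | 28 / 27 | 23 / 22 |
| Overall change | either | 5 | 5 | 5 |

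With a reference-group drift of 2 points, the lowest increase or decrease figure is 19% and overall change reaches at most 8%. With a drift of 3 points these become 17% and about 10%. If 15–30% of people have exactly no change, increase or decrease lies at 32–37% (SD 4.37, 50:50).

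**7. Numbers for 80% power (SD 4.37, 50:50).** About 600 in total on the continuous score and about 950 on increase or decrease. The second exceeds the whole pool of 723.

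**The case against.** The strongest reply is that the article claims no power for associations. It ties 150 to change over time, calls the objective exploratory, and works from a capped pool, so no calculation could have altered recruitment. That stands, and so does the point that an article may leave SD, alpha and power to a fuller document. Their absence is not the fault here; it only means the figures above are illustrations.

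A reader might infer that the overall-change contrast cannot find a directional factor at all. That goes too far. It follows from change spread symmetrically about zero. A simulation with about 40% of people at score 0 at baseline, a drift of 1 point and an SD of change of 3.9–4.2 (assumptions, not document figures) gave overall-change power of about 13%, 46% and 81% for effects of 1, 2 and 3 points. The increase and decrease contrasts also stand beside it, so a directional factor has two other places to appear.

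The gain from a continuous outcome also varies. In those floor-bounded runs, with a drift of 1–2 points and a 1-point effect, it had 43–47% power against 39–40% for increase. The gain is real but modest there.

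Finally, the contrasts are introduced as change in categories, which could mean movement between the none, low, medium and high bands. The proportions above would then differ, but the pooling of opposite directions would remain.

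**Conclusion.** The point holds in a limited form. The 150 supports the mean change over time and nothing else, and the association analysis is set on outcomes that discard information. Reducing the score to yes/no and pooling opposite directions are weaknesses of the chosen outcomes whatever the SD. Their size is conditional: about 49–71% power on the continuous score for a 50:50 factor, about 20–50% for increase or decrease across 50:50 to 20:80, and about 5–10% for overall change, higher with a floor or a larger effect. All of this rests on an SD back-solved from 150, a borrowed 1-point group difference and roughly normal change.

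Two stronger readings are not supported. One is that any single power figure, such as 40% or 5%, is a fact about this study; the article fixes none of the inputs. The other is that the plan presents 361 as sufficient for the factors of change; it does not say so, though a reader could take the unqualified comparison of 361 with 150 that way.

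**What to change.** **Statistical analyses.** Make the signed raw MTBQ score the outcome of the association analysis. The linear mixed model already named suits this: repeated scores with a factor-by-time term, or the change score, with robust or bootstrap intervals for skew. Adjustment for baseline score should be a sensitivity analysis only. The Introduction reports that health literacy, finances, number of conditions and medications were associated with burden at baseline, and adjusting for an error-prone baseline correlated with exposure can bias the association. Keep increase and decrease as descriptive groups, and drop overall change against no change as an association outcome.

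**Sample size.** Say that 150 refers to a mean change of 1 raw point over time only. One point is the smallest step for one person, not for a group mean. Add, with its assumptions, the between-group difference detectable with 361 at 80% power, 2.802 × SE under the two-sided implied SDs:
- 50:50 factor: 2.802 × 0.398 to 0.460, about 1.1 to 1.3 raw points
- 20:80 factor: 2.802 × 0.497 to 0.575, about 1.4 to 1.6 raw points

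**Cost.** Wording in two sections and a regression on data already to be collected. Results come in score points rather than proportions who rose or fell, and the sample-size position looks less favourable. Power for a 1-point group difference stays below 80% even then.
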